**- Collection, processing, preservation, and analysis of biological samples.**

In each patient, prior to coronary angiography and the administration of any drug necessary for the coronary angiography, especially heparin required for coronary procedures, as well as iodinated contrast; a 6 mL blood collection (EDTA K2 tube) will be performed. Plasma sample collection and preparation will be performed according to NCI (USA) standard operating procedures. Samples will be stored in the IRBLleida Biobank belonging to the National Biobank Platform. The specific analysis of miRNAs will be performed in the TRRM group laboratory of the Institut de Recerca Biomèdica de Lleida. The analysis of the the rest of biochemical and/or hematological parameters will be performed in the laboratories of the University Hospital Arnau de Vilanova of Lleida. If no differences are observed between miRNAs in the different study groups, the samples will be kept in the IRBLleida Biobank for the assessment of other biomarkers in which the TRRM group has experience, such as lncRNAs, circRNAs, proteins, etc., and for the analysis of the other biomarkers in which the TRRM group has experience, such as lncRNAs, circRNAs, proteins, etc., in the IRBLleida Biobank.

RNA isolation and miRNA quantification will be performed by experienced personnel without access to clinical data. All experiments will be performed using the gold-standard technique; RT-qPCR, under standardized conditions in the same laboratory and according to the previous methodology used by the research group (50–52). Briefly, total RNA will be isolated from 200 μL of frozen plasma samples using the miRNeasy Serum/Plasma Advanced kit (Qiagen) according to the manufacturer's instructions. *Caenorhabditis elegans* miR-39-3p synthetic RNA (cel-miR-39-3p) will be added as external reference RNA. RNA purification will be performed with RNeasy UCP MinElute centrifugation columns according to the manufacturer's recommendations. RNA will be stored in a -80 °C freezer until further analysis. RT-qPCR analysis will be performed according to the recommendations of the MIQE guidelines (53). miRNA quantification will be performed according to the protocol of the miRCURY® LNA® RT Kit (Qiagen) system, which offers optimal accuracy and reproducibility (54). RT reactions will be performed using the miRCURY LNA RT kit (Qiagen). The cDNA will be stored at -20°C. Quantitative PCR (qPCR) will be performed with the miRCURY LNA SYBR® Green PCR kit (Qiagen) using 384-well miRCURY LNA miRNA custom PCR Panels (Qiagen). The qPCR will be performed on a QuantStudio ™ 7 Flex real-time PCR system (Thermo), followed by melting curve analysis. The qPCR amplification curves will be evaluated with QuantStudio Software v1.3 (Thermo). A Cq greater than 35 cycles will be considered undetectable and censored at the minimum level observed for each miRNA. MiRNAs where 80% of the samples meet these criteria will be considered below the detection limit. Relative quantification will be performed using the 2-dCq method, where:

| ΔCq = Cq_miRNA_ − Cq_cel-miR-39-3p_. |
| --- |

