**HYPOTHESIS**

Different patterns of coronary artery involvement are associated with the overexpression or underexpression of specific miRNAs.

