**- Sample size estimation.**

Based on previous studies of our group and previous studies for the determination of miRNAs in the presence of coronary endothelial dysfunction, we have recruited around 40-50 patients to complete the investigation (7,48–50). In our case, we will study the relationship between miRNAs and the different patterns of involvement according to the affected coronary compartment, that is, Group 1 (Macrovascular and Microvascular Angina); Group 2 (Macrovascular Angina); Group 3 (Microvascular Angina); and Group 4 (Non-coronary chest pain). Given that Group 4 corresponds to patients without coronary circulation alterations, it will be used as a control group with respect to the other groups until recruitment of 25 patients per group is completed, in a similar amount to other control groups in similar studies, totaling 100 patients. Likewise, given the possibility that some patients may present macrovascular and/or microvascular spasms that could overlap with some of the other groups, Group 5 (Macrovascular or Microvascular Spastic Angina) has been defined and will not be included for the purposes of estimating the sample size.

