**- Statistical analysis.**

Continuous variables will be expressed as mean ± standard deviation (SD) or median with interquartile range (IQR), according to their distribution. As appropriate, the Mann-Whitney U test will be used to compare continuous variables, while the Chi-square test or Fisher's test will be used to compare categorical variables. If subgroup studies within each group are required (example: patients in group 1 [macrovascular angina and microvascular angina] and diabetes), the Factorial ANOVA test will be performed when equal variances are assumed or the Brown Forsythe test when unequal variances are assumed, followed by post hoc analysis with Bonferroni correction for multiple comparisons. Results will be shown as mean with a 95% confidence interval (CI). The equality of variances between groups will be calculated for each dependent variable using the Leven test, with Bonferroni correction to test for homogeneity of variance between all levels of comparison.

An alpha level of 0.05 will be used to assess statistical significance. Data will be analyzed using SPSS software or STATA.

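### A detection filter pooled over all groups can remove a miRNA detected in up to 20 of 25 patients of one group, and fill-in at the minimum shrinks mean differences and SDs

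*Protocol*

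**What the plan says.** The Protocol section on collection, processing, preservation and analysis of biological samples sets two rules. For single values: "A Cq greater than 35 cycles will be considered undetectable and censored at the minimum level observed for each miRNA". For whole miRNAs: "MiRNAs where 80% of the samples meet these criteria will be considered below the detection limit". The second rule does not mention groups. It does not say whether 80% means at least or more than 80%, or whether Group 5 samples count. Quantification is relative, on the 2^-ΔCq scale.

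The sample size section recruits "until recruitment of 25 patients per group is completed, in a similar amount to other control groups in similar studies, totaling 100 patients". The spastic group comes on top of this: "Group 5 (Macrovascular or Microvascular Spastic Angina) has been defined and will not be included for the purposes of estimating the sample size".

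In the statistical analysis section, "the Mann-Whitney U test will be used to compare continuous variables". For subgroup studies, "the Factorial ANOVA test will be performed when equal variances are assumed or the Brown Forsythe test when unequal variances are assumed", and results are then shown as means with 95% confidence intervals.

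The hypothesis is: "Different patterns of coronary artery involvement are associated with the overexpression or underexpression of specific miRNAs".

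**The concern.** The study looks for miRNAs that behave differently in different groups. A filter that looks only at the pooled share of undetectable samples cannot tell a miRNA that is faint everywhere from one that is clearly present in one group and absent in the rest. With four equal groups, one group is a quarter of the samples, so a one-group signal starts at 75% undetectable even with perfect detection. Only five points remain before the threshold. A strong contrast could be set aside before any test is run.

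The fill-in raises a separate issue. Giving every undetectable sample the same value treats a bound as a measurement. The more values are filled in, the closer the group means move together and the smaller the SDs become. This matters wherever the protocol uses means: the reported means with intervals, and the subgroup ANOVA.

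**Working it through.** **Inputs from the protocol.** 4 groups × 25 = 100, which reproduces the stated total. The filter threshold is 80% of samples and the detection cut-off is Cq 35. The size m of Group 5 is not fixed.

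**Assumptions, not in the protocol.** Detection rates, the size of the group difference and the SD.

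**1. Where the filter bites.** Let d be the number detected in the one expressing group, with none detected elsewhere. Without Group 5, the undetectable share is (100 − d)/100.

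| d of 25 | Undetectable | Result |
|---|---|---|
| 25 | 75% | kept |
| 21 | 79% | kept |
| 20 | 80% | lost under 'at least 80%' |
| 19 | 81% | lost on either reading |
| 10 | 90% | lost on either reading |

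Fisher's exact test for the contrasts that would be lost, one group against the other 75 patients:
- 20/25 v 0/75: p about 1e-16
- 19/25 v 0/75: p about 1.3e-15
- 10/25 v 0/75: p about 2e-7

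**2. How often a one-group signal is lost.** With X ~ Binomial(25, p), loss is X ≤ 20 ('at least 80%') or X ≤ 19 ('more than 80%'). The last column adds 5% background detection in the other 75 patients, under 'at least 80%'.

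| Detection rate p | At least 80% | More than 80% | At least 80%, 5% background |
|---|---|---|---|
| 90% | 9.8% | 3.3% | 0.7% |
| 80% | 57.9% | 38.3% | 11.6% |
| 70% | 91.0% | 80.7% | 40.2% |
| 60% | 99.1% | 97.1% | 71.8% |

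If two groups share the marker, X ~ Binomial(50, p) and loss is again X ≤ 20. The chance is 7e-10 at 80% detection, 1e-5 at 70%, 0.3% at 60% and 10% at 50%.

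**3. Group 5 in the denominator.** With 25/25 detected in one group and m Group 5 samples, none of them detected, the undetectable share is (75 + m)/(100 + m). This reaches 80% at m = 25 (100/125). From then on, even complete detection in one group is lost under 'at least 80%'.

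**4. Fill-in.** Assume log2 levels N(0, 1.5) and N(1, 1.5), a two-fold difference. Take the filled-in level as the detection threshold c, chosen to give the stated average share undetectable. The filled-in log2 difference is E[max(X₁, c)] − E[max(X₀, c)]. The 2^-ΔCq column applies the same fill-in to 2^X.

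| Undetectable | log2 difference (true 1.0) | Share of the difference kept on 2^-ΔCq |
|---|---|---|
| 20% | 0.81 | 97% |
| 40% | 0.60 | 91% |
| 60% | 0.40 | 79% |
| 75% | 0.24 | 64% |

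SDs shrink as well. In a simulation of 25 v 25 with a 0.8 SD shift, the pooled log-scale SD falls from 1.0 to about 0.85, 0.69 and 0.53 at 25%, 50% and 70% undetectable in the lower group.

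**5. Mann-Whitney.** In the same simulation, power without and with fill-in is 76.6% and 76.6%, 75.6% and 72.5%, and 77.5% and 67.6% at those three levels.

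**The case against.** A reader might infer that any miRNA expressed in only one group is discarded. The arithmetic does not support that: with Groups 1 to 4 alone, detection in 21 to 25 of 25 patients is kept, and the 20/25 case is lost only if 80% means at least 80%.

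Nor are compartment markers in general at risk. Group 1 has both compartments affected, so a macrovascular marker may appear in Groups 1 and 2 and a microvascular marker in Groups 1 and 3. Such a marker is almost never lost at detection rates of 60% or more. A miRNA underexpressed in one group is safe if the others express it. The section on scientific interest also anticipates gradients by number of compartments, not only all-or-none patterns.

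A reader might further infer that fill-in biases the main group comparison. It does not bias a mean there: Mann-Whitney is rank based, fill-in at the minimum keeps undetectable values at the bottom, and the cost is ties and some power. The choice between ΔCq and 2^-ΔCq makes no difference to it. ANOVA is limited to subgroup studies, and the section allows medians with IQR according to distribution. On the 2^-ΔCq scale the loss in the mean difference is modest until non-detection is heavy.

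Finally, the protocol does not say in words that a miRNA below the detection limit is dropped from analysis, although no other consequence is given.

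All of this stands and narrows the point. It does not remove it. A miRNA partly detected in a single group (10/25 v 0/75, for instance) is lost on either reading of 80%, and the protocol itself fixes the rule.

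**Conclusion.** The point holds in limited form. As written, the filter can remove a strong one-group signal when detection in that group is incomplete: at most 20 of 25 patients, or 19 if the rule means more than 80%. The cut-offs follow from the group sizes alone. The chances of loss (10%, 58%, 91% and 99% at 90%, 80%, 70% and 60% detection) assume no detection elsewhere and fall quickly with background detection or a shared marker. The unstated role of Group 5 could make the filter stricter still.

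For retained miRNAs, fill-in shrinks mean differences and SDs. Under an assumed two-fold difference and log2 SD of 1.5, 81% to 24% of the log2 difference remains as non-detection rises from 20% to 75%, against 97% to 64% on the 2^-ΔCq scale. This bears on reported means, their intervals and subgroup ANOVA. The Mann-Whitney comparison is largely unaffected, with 0 to about 10 points of power lost in the cases simulated.

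**What to change.** - **Filter.** Class a miRNA as below the detection limit only if at least 80% of samples are undetectable in every one of Groups 1 to 4, and state that Group 5 does not enter that denominator. A miRNA is then kept once 6 of 25 are detected in any one group (19/25 = 76% undetectable). At a 50% detection rate in one group only, the chance of being kept rises from about 0.05% to 99.8%. State also that a miRNA so classed is left out of the comparisons, if that is the intent.
- **Multiplicity.** A filter that looks at groups is not independent of the group test. Whatever adjustment is used should therefore count every listed miRNA and every added candidate, filtered or not.
- **Analysis.** Keep Mann-Whitney as the group comparison. Set in advance what share of non-detection counts as substantial. For miRNAs above it, report detection rates by group with Fisher's exact test, and replace means of filled-in values with medians, or give a left-censored model on ΔCq as a sensitivity analysis.

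The change is to wording only and needs no further patients, samples or assays. The cost is that a few more low-expressed miRNAs are tested and the analysis takes slightly more work.

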**- Bioinformatics analysis.**

It will be performed according to previous publications of the research group (25) . The molecular pathways affected by the identified transcripts will be analyzed using the web-based computational tool DIANA-miRPath v3.0 that combines estimates and experimental data with the KEGG tool to identify molecular pathways.

**- Design**

Illustration 2. Explanatory diagram of the Clinical Phase.

**- Diagnostic coronary angiography and physiological evaluation of the coronary tree.**

After diagnostic coronary angiography, a standardized analysis of coronary lesions in terms of percentage of stenosis and length of the lesion will be performed by quantitative coronary angiography (QCA), in order to avoid variability in visual estimation of coronary lesions. Subsequently, a functional assessment of epicardial lesions with a pressure guidewire will be performed, first with the measurement of nonhyperemic coronary indexes: "Resting full-cycle ratio" (RFR) and RFR adjusted for discordance predictors ("Adjusted RFR), and then by means of the hyperemic coronary indices "Fractional Flow reserve" (FFR), "Coronary Flow Reserve" (CFR) and "Index of Microcirculatory Resistance" (IMR) positioning the pressure guidewire in the distal segment of each artery to be evaluated, being able to interrogate more than one artery in the same patient. Similarly, in patients referred for coronary angiography who have a previous positive ischemia test and whose epicardial arteries are not considered tributary to evaluation, the pressure guide wire will also be placed in the artery corresponding to the territory compatible with the ischemia detected in the test. In the case of coronary lesions not susceptible to physiological evaluation, the pressure guide wire will be positioned in the distal segment of the anterior descending artery, evaluating the "Coronary Flow Reserve" (CFR) and the "Index of Microcirculatory Resistance" (IMR) in the territory of the anterior descending artery. Measurements will be obtained using the ″PressureWire™ X Guidewire 0.014" device (Abbott Vascular Inc., Santa Clara, CA,). For induction of hyperemia, adenosine will be used as a vasodilator drug. In addition, for each lesion the angiography-derived index "Quantitative Flow Ratio" (QFR) and for each artery the "Angiography-derived Index of Microcirculatory Resistance" (IMRangio) will be evaluated.

As for the performance of the coronary vaso-reactivity test, acetylcholine will be used as described above. Given the risk of epicardial spasm in case of macrovascular ischemia derived from epicardial lesions, the acetylcholine test will be performed only in patients who do not present pathological FFR values (> 0.80). More detailed recommendations for the performance of coronary physiology studies are presented in **Annex 2**.

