**- Determination of the affected coronary pattern.**

Once the parameters have been obtained, the angina pattern corresponding to each patient will be determined, based on the values of FFR, CFR and IMR, and the treatment corresponding to the findings obtained will be carried out. The decision of medical, percutaneous, or surgical treatment of epicardial coronary lesions leading to ischemia will be made on the basis of FFR.

Macrovascular involvement will be defined when the FFR value is ≤ 0.80 and microvascular involvement when the IMR value is ≥ 25 or the CFR is < 2.0 in the presence of an FFR > 0.80. Angina patterns will depend on the different combinations according to coronary compartment involvement, namely Group 1 (Macrovascular and Microvascular Angina); Group 2 (Macrovascular Angina); Group 3 (Microvascular Angina); and Group 4 (Noncoronary Chest Pain). Since the present protocol also considers an approach to the study of coronary spasm, an additional group will be considered, through the evaluation of the acetylcholine test in patients presenting microvascular angina or noncoronary chest pain (Groups 3 and 4). Patients presenting macro or microvascular spasm in this test will be included in Group 5 (Macro or Microvascular Spastic Angina).

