| **Positioning of the Pressure-Temperature Guide**  • For the evaluation of epicardial lesions (RFR and FFR), the pressure sensor should be placed distal to the main vessel to be analyzed.  • RFR is measured first, followed by FFR, CFR, and IMR.  • For the determination of CFR and IMR, the pressure sensor should be placed in the distal segment of the vessel corresponding to the lesion to be evaluated.  • In the case of patients referred for coronary angiography who present a positive ischemia test, FFR, CFR and IMR will also be measured, in addition to the arteries of the lesions to be evaluated, in the arteries compatible with the ischemia detected in the ischemia test. Likewise, in the absence of lesions to be evaluated and a previous positive ischemia test to guide the exploration, the FFR, CFR and IMR will be evaluated in the anterior descending artery.  • A second guidewire, in addition to the pressure guidewire, could cause artifacts and should therefore be avoided.  • Detect artifacts: the sensor could interact with the wall of the vessel, especially in cases of narrow vessel caliber or severe tortuosity.  • Viscous contrast agent in the coronary artery may affect the pd/pa gradient. |
| **Hyperemia**  • Before advancing the pressure wire, administer nitroglycerin ic (usually 200 mcg) to prevent coronary spasm.  • Medications for hyperemia.  - Intravenous adenosine 140 μg / kg / min.  • In case of measurement results in the borderline area, an increase in the dose of ev adenosine is possible. However, intravenous doses> 180 μg / kg / min may reduce coronary perfusion and are therefore not recommended. |

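### The methods and Annex 2 disagree on when the default LAD is used and whether FFR is taken there, and no rule turns several arteries into one patient group

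*Protocol*

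**What the plan says.** The Protocol's section on diagnostic angiography and physiological evaluation sets a default artery: "In the case of coronary lesions not susceptible to physiological evaluation, the pressure guide wire will be positioned in the distal segment" of the LAD, "evaluating the 'Coronary Flow Reserve' (CFR) and the 'Index of Microcirculatory Resistance' (IMR) in the territory of the anterior descending artery". FFR is not in that list.

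Annex 2, under positioning of the pressure-temperature guide, also sends the wire to the LAD by default, but "in the absence of lesions to be evaluated and a previous positive ischemia test to guide the exploration". In that case "the FFR, CFR and IMR will be evaluated in the anterior descending artery".

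The methods section allows several arteries, "being able to interrogate more than one artery in the same patient". Annex 2 adds arteries in the territory of a positive ischaemia test to those carrying lesions.

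The section on determining the affected pattern then works at patient level: "the angina pattern corresponding to each patient will be determined, based on the values of FFR, CFR and IMR". Macrovascular involvement is FFR ≤ 0.80. Microvascular involvement is IMR ≥ 25 or CFR < 2.0, with a condition of FFR > 0.80. Access to the spasm test depends on FFR too: "the acetylcholine test will be performed only in patients who do not present pathological FFR values (> 0.80"). The sample size section counts recruitment by group, 25 in each of Groups 1 to 4, with Group 4 as control.

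**The concern.** The group label is the exposure in the primary objective and the unit in which recruitment is counted. Two features of the text leave it open.

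- **Default LAD.** The two descriptions differ in what triggers the default and in which indices are taken. The grouping rule cannot be applied without FFR. Under the methods wording, a patient whose lesion in another artery was not evaluated could also be labelled from LAD readings alone. If those are normal, that patient could be counted as a control.
- **Several arteries.** Each artery has its own FFR, CFR and IMR, and the patient gets one label. The text does not say which artery counts or how discordant arteries combine. Patients with more arteries tested also have more chances of an abnormal reading under some rules. Group membership could then partly reflect how much was measured. That matters for the gradient by number of compartments affected, which the scientific interest section hopes to assess.

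**Working it through.** The plan gives no figure to reproduce here. Its total of 100 is 4 × 25 and carries no information on artery-level results. The check is textual, followed by an enumeration of the grouping rule.

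**Step 1. The two default rules side by side.**

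| | Methods section | Annex 2 |
| --- | --- | --- |
| Trigger | Lesions that are not amenable to physiological evaluation | No lesion to evaluate and no positive ischaemia test |
| Indices named in the LAD | CFR, IMR | FFR, CFR, IMR |

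**Step 2. The grouping rule with FFR missing.** The condition FFR > 0.80 can be read as governing both IMR and CFR (reading A) or CFR only (reading B). Letting the unknown FFR fall on either side of 0.80 gives these possible groups:

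| CFR < 2.0 | IMR ≥ 25 | Reading A | Reading B |
| --- | --- | --- | --- |
| no | no | 2 or 4 | 2 or 4 |
| no | yes | 2 or 3 | 1 or 3 |
| yes | no | 2 or 3 | 2 or 3 |
| yes | yes | 2 or 3 | 1 or 3 |

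No row gives a unique group. In every row, one candidate is a group that Annex 2 makes eligible for acetylcholine (3 or 4) and the other is not (1 or 2). Access to that test is therefore undetermined as well.

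**Step 3. Two arteries.** Three yes/no indices give 2 × 2 × 2 = 8 states per artery, and 8 × 9 / 2 = 36 unordered pairs.

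- Reading A: 4 states fall in Group 2, 3 in Group 3 and 1 in Group 4. Pairs in different groups: 4×3 + 4×1 + 3×1 = 19 of 36.
- Reading B: 2 states fall in Group 1, 2 in Group 2, 3 in Group 3 and 1 in Group 4. Pairs in different groups: 2×2 + 2×3 + 2×1 + 2×3 + 2×1 + 3×1 = 23 of 36.

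These count logical states, not patients.

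**Step 4. One worked patient.** Artery 1 has FFR ≤ 0.80 with normal CFR and IMR, which is Group 2. Artery 2 has FFR > 0.80 and IMR ≥ 25, which is Group 3. If any abnormal artery counts for its compartment, the patient is Group 1. All three labels are compatible with the text.

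**Step 5. Consequence for Group 1.** Under reading A, no single artery can be both macrovascular and microvascular. Group 1 then exists only through a rule that combines arteries, and the protocol does not state one.

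**The case against.** The best defence is that the protocol should be read as a whole. The methods paragraph does not say that CFR and IMR are the only indices taken, and it refers to Annex 2 for detail. Annex 2 opens by listing FFR among the measurements and repeats it for the default LAD. Distal pressure at hyperaemia is needed for IMR in any case (IMR = Pd × Tmn), so FFR is probably obtainable. This stands as far as it goes. A reader might infer that these patients cannot be grouped at all, and the documents do not support that: under Annex 2 they can be. The differing text and triggers remain.

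A second defence is that the methods trigger may be a translated phrase for lesions that do not warrant evaluation, which would match Annex 2. Exclusion criterion 7 also removes total occlusions that prevent measurement. Both points narrow the problem. Neither settles it, because the criterion does not cover other unevaluated lesions and the wording bears either meaning.

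Third, discordant arteries do not make a patient ungroupable, and the acetylcholine condition hints at an any-artery reading for FFR. That is right, but it says nothing about IMR or CFR.

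Fourth, an analysis plan might define the patient-level variable. Here the label acts earlier: it decides who is tested for spasm and when a group is full. An analysis plan cannot restore an FFR that was not recorded.

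**Conclusion.** The point holds as an internal contradiction plus an unfixed rule, both in the construction of the primary comparison groups. If the methods text is followed alone, the label is ambiguous in all 4 combinations of CFR and IMR. With two discordant arteries, the same patient can be Group 1, 2 or 3.

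The number of patients affected cannot be computed. The document gives neither the share of patients reaching the default LAD nor the number of arteries tested per patient. It is plausible that default-LAD patients supply much of Groups 3 and 4, but that is an inference.

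A reader might also want to state a rate at which abnormal labels rise with each extra artery. That would need a per-artery prevalence and the correlation between arteries of one patient, and the protocol gives neither. Nor does the text support taking the lowest-FFR artery as the evident index artery. Under reading A that choice would leave Group 1 empty. It would also leave the macrovascular label as dependent on testing intensity as before, since the lowest FFR is ≤ 0.80 exactly when any FFR is.

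This should be corrected. It is not a reason to hold that the study cannot be run.

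**What to change.** 1. Reconcile the physiological evaluation section, the pattern determination section and Annex 2 on the trigger for the default LAD and on the indices obtained there. The FFR that the grouping rule requires should exist for every grouped patient.
2. Reconcile the acetylcholine passages at the same time, since they read the same FFR. This review does not say which clinical rule is right.
3. For the research grouping, do not count a patient with an unevaluated lesion as a Group 4 control.
4. Before enrolment, fix one patient-level rule for combining arteries. It must be compatible with Group 1 existing, so the scope of the FFR > 0.80 condition has to be made explicit. Name an alternative rule as a sensitivity analysis.
5. Report the number of arteries tested by group, so that readers can judge whether labels follow testing intensity.

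The cost is a short amendment. No extra procedure is needed for the FFR value, because hyperaemic distal pressure is already recorded for IMR.
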